**LIST OF ABBREVIATIONS**

|         |                                                    |
|---------|----------------------------------------------------|
| AE      | Adverse Event                                      |
| ALP     | Alkaline Phosphatase                               |
| ALT     | Alanine Aminotransferase                           |
| AST     | Aspartate Aminotransferase                         |
| BUN     | Blood Urea Nitrogen                                |
| CBC     | Complete Blood Count                               |
| CI      | Confidence Interval                                |
| cm      | centimeter                                         |
| CMP     | Comprehensive Metabolic Panel                      |
| CRF     | Case Report Form                                   |
| °C      | Degrees Celsius                                    |
| D       | Day                                                |
| EDTA    | Ethylenediaminetetraacetic acid                    |
| EIA     | Enzyme Immunoassay                                 |
| EID     | Egg Infectious Dose                                |
| ELISPOT | Enzyme-Linked Immunosorbent Spot                   |
| ENT     | Ear Nose and Throat                                |
| FSUE    | Federal State Unitary Enterprise                   |
| GCP     | Good Clinical Practice                             |
| GMT     | Geometric Mean Titer                               |
| HA      | Hemagglutinin                                      |
| HAI     | Hemagglutination Inhibition                        |
| HBsAg   | Hepatitis B Surface Antigen                        |
| HBV     | Hepatitis B Virus                                  |
| hCG     | human Chorionic Gonadotropin                       |
| HCV     | Hepatitis C Virus                                  |
| HIV     | Human Immunodeficiency Virus                       |
| ICF     | Informed Consent Form                              |
| ICH     | International Conference on Harmonization          |
| ICMJE   | International Committee of Medical Journal Editors |
| IEC     | Independent Ethics Committee                       |
| IEM     | Institute for Experimental Medicine                |
| IgA     | Immunoglobulin class A                             |
| IgG     | Immunoglobulin class G                             |
| IRB     | Institutional Review Board                         |
| l       | liter                                              |
| LAIV    | Live Attenuated Influenza Vaccine                  |
| MDCK    | Madin-Darby Canine Kidney                          |
| mg      | milligram                                          |
| ml      | milliliter                                         |
| mm      | millimeter                                         |
| MoH     | Ministry of Health and Social Development          |
| MoP     | Manual of Procedures                               |
| n       | number (typically refers to number of subjects)    |

|        |                                                           |
|--------|-----------------------------------------------------------|
| NA     | Neuraminidase                                             |
| PBMC   | Peripheral Blood Mononuclear Cell                         |
| PI     | Principal Investigator                                    |
| PCR    | Polymerase Chain Reaction                                 |
| PVS    | PATH Vaccine Solutions                                    |
| RBC    | Red Blood Cell                                            |
| RF     | Russian Federation                                        |
| RII    | Research Institute of Influenza                           |
| RNA    | Ribonucleic Acid                                          |
| rRTPCR | Real-time Reverse Transcriptase Polymerase Chain Reaction |
| SAE    | Serious Adverse Event                                     |
| SMC    | Safety Monitoring Committee                               |
| SOP    | Standard Operating Procedure                              |
| TCID   | Tissue Culture Infectious Dose                            |
| US     | United States                                             |
| WBC    | White Blood Cell                                          |
| WHO    | World Health Organization                                 |

## 2 Background Information and Scientific Rationale

### 2.1 Background Information

Vaccines are the most important intervention for the control and prevention of influenza and for reducing morbidity and mortality. Effective vaccines against avian A (H5N1) and other avian influenza viruses are a high public health priority. Production of live-attenuated and inactivated vaccine seed viruses against avian influenza viruses, which have the potential to cause pandemics, may establish proof of concept and will increase manufacturing experience that will be critical in the event of the emergence of such a virus into the human population. The observed efficacy of live-attenuated vaccines for human inter-pandemic influenza, together with findings to date that inactivated or subunit avian influenza vaccines are suboptimally immunogenic in humans, strongly suggest that use of live-attenuated influenza vaccines (LAIVs) against pandemic influenza are worth exploring. LAIVs have higher yields and simpler manufacturing processes as compared to inactivated vaccines, may provide superior immunogenicity in seronegative populations, and have the potential to elicit broader immune responses than inactivated or subunit vaccines. Since LAIVs are generally delivered via intranasal inoculation, another appealing aspect of this approach in a pandemic situation is a simplified, needle-free delivery system. Because LAIV technology requires less complex downstream processing than inactivated vaccines, WHO considers LAIVs to be possibly more appropriate for production of pandemic influenza vaccines and thus, the WHO Global Action Plan encourages increased development, production and technology transfer of LAIV.

From the policy perspective, the decision to use a live-attenuated vaccine prior to a pandemic would be partially influenced by characteristics of the vaccine strain and concerns for reassortment with circulating influenza strains. Such a reassortment event would be particularly concerning for an A/H5N1 strain, for example, which has a demonstrated high case-fatality rate, but is not yet circulating widely and has not acquired the ability to transmit efficiently from person-to-person. Thus, it is important to understand the characteristics of potential pandemic vaccines based on avian strains, to understand their immunogenicity and reactogenicity in humans, and to understand their shedding characteristics, the latter of which could influence their propensity to reassort with circulating human strains.

LAIVs have been used for seasonal influenza vaccines for over 40 years in Russia. The Institute of Experimental Medicine (IEM) in St. Petersburg has been collaborating with PATH Vaccine Solutions (PVS), a nonprofit corporation that is a supporting organization of the nongovernmental global health organization, PATH, to develop prototype live-attenuated cold-adapted reassortant pandemic influenza vaccines based on avian strains. The overall plan includes the generation of a set of live-attenuated cold-adapted reassortant viruses bearing an H5N1 and H7N3 on the attenuated A/Leningrad/134/17/57 (H2N2) master donor strain background. The cold-adapted, live monovalent A/17/mallard/Netherlands/00/95 (H7N3) influenza vaccine will be tested in this study. The virus strain in this vaccine was constructed in the laboratories of IEM by classical reassortment of

A/mallard/Netherlands/12/00(H7N3) virus with a cold-adapted temperature sensitive A/Leningrad/134/17/57(H2N2) virus master strain in developing chicken embryos. The 6:2 genomic reassortant was characterized for acceptable phenotype and genotype [presence of cold-adapted, temperature sensitive, hemagglutinin (HA), and neuraminidase (NA) markers], with genetic sequencing used to confirm the molecular basis of the attenuated phenotype. The developed vaccine strain was transferred to Microgen to produce a bulk lot of vaccine for use in preclinical immunogenicity and challenge studies and for use in clinical trials. Additional information on the development and preclinical testing of this candidate vaccine may be found in the Confidential Investigator's Brochure.

The World Health Organization (WHO) acknowledged advantages of LAIV use compared to inactivated vaccine in case of pandemic events. The main goal stated by WHO in the Global Influenza Preparedness Plan was to establish a collection of prepandemic influenza vaccines which could be used as a basis for vaccine manufacturing in a pandemic situation.

In September of 2003 at an international workshop on pandemic influenza vaccines hosted by the United States National Institutes of Health, a clinical trial plan for pandemic influenza vaccines was developed and levels of priority for evaluation of different influenza candidate vaccine strains were proposed. Influenza H1, H2 and H3 virus subtypes were evaluated as belonging to the "highest priority" level, and influenza viruses of H5, H6, H7 (such as that proposed in this trial), and H9 subtypes were assigned to a "high priority" level. In addition to this, the importance of our proposed trial is supported by WHO's decision to include LAIVs in the WHO global action plan to increase vaccine supply for influenza vaccines.

Prior clinical trials have demonstrated that the Russian monovalent LAIV "Ultragrivac" (manufactured by Microgen) based on 7:1 reassortant of A/duck/Potsdam/1402-6/86 (H5N2) apathogenic avian influenza virus with A/Leningrad/134/17/57 (H2N2) master donor virus was well-tolerated and immunogenic in healthy adult volunteers. Results showed that the vaccine was minimally reactogenic, safe and genetically stable. The seroconversion rate after two doses of the vaccine, defined by a four-fold rise in HAI titre, was approximately 50%. Based on these promising results, WHO stated that avian-human reassortants with the Leningrad 17 strain deserve additional study.

Also of importance is that the Russian LAIV, based on a 6:2 reassortant of A/PR/8/34 (H1N1) with the master donor strain, has been shown in studies in mice to induce not only humoral responses, but also cellular immune responses at the initial site of infection, including CD4+, CD8+ and CD19+ responses.

A number of LAIVs, derived from cold-adapted A/AnnArbor/6/60 ca (H2N2) Master Donor Virus (MDV-A; Medimmune, Gaithersburg, MD, USA) and avian influenza virus strains containing H5, H6, H7, and H9, have been produced and tested in healthy adult volunteers in phase I trials in the United States. All candidates were well-tolerated. However, these LAIVs were highly restricted in replication in healthy seronegative adults and induced variable immune responses. The seroconversion rates after two doses of the vaccine, defined by a four-fold rise in HAI titre, were 92% for Medimmune's H7N3 candidate, 62% for the H9N2 candidate, 0-10% for two different H5N1 candidates (one of which was produced at different virus doses), and 5% for the H6N1 candidate. Although HAI seroconversion rates

were moderate for some of the candidate vaccines, mean HAI titres were consistently low. Interestingly, serum IgA responses appeared to be most consistent measure of an immune response in these studies. In summary, live attenuated influenza vaccines based on H7N3, H9N2, H6N1 and H5N1 avian viruses and the American A/Ann Arbor/6/60ca (H2N2) master donor virus were also well tolerated but displayed varying degrees of immunogenicity.

## **2.2 Dose Rationale**

According to the WHO data influenza A/H7N3 virus is a potentially pandemic subtype to which the human population is immunologically “naïve”, i.e., has no preexisting antibodies to this agent and lacks immune memory against the said virus. Results obtained by the FSUC “SIC Microgen” MOHSD RF within clinical evaluation of pre-pandemic (H5N1) and pandemic (H1N1) live influenza vaccines showed inability of single-dose vaccination to generate adequate protective immune responses in “naïve” humans. Hence, in this study volunteers will be immunized with two doses given intranasally 28 days apart (by delivery of 0.25 ml into each nasal passage).

## **2.3 Potential Risks and Benefits**

### **2.3.1 Potential Risks**

#### **2.3.1.1 To Participant Well-Being**

Administration of study vaccine or placebo may cause the subject only mild discomfort or a tickling sensation in the nasal passages. The study vaccine to be used for this trial is produced by the same classical reassortant method as is seasonal trivalent LAIV currently approved for use in Russia; therefore, side effects may be similar. These may include, minimally, mild flu-like symptoms. The avian influenza virus strain [A/mallard/Netherlands/12/00(H7N3)] utilized to construct the study vaccine virus, is a low-pathogenicity strain. Moreover, it has been reassorted with the same cold-adapted master strain [A/Leningrad/134/17/57(H2N2)] utilized to construct seasonal LAIV. All attenuation mutations have been confirmed by molecular sequencing and attenuated phenotype was confirmed through preclinical testing in animals (See Confidential Investigator’s Brochure). Thus, no increased pathogenicity is expected in humans. The World Health Organization’s Quality, Safety and Standards department considers the likelihood of direct harm from reassortants derived from H5 or H7 strains in which the multiple basic amino acid cleavage site has been removed to be “very remote.” However, serious or allergic reactions may be possible. These might include symptoms of pneumonia in the unlikely event that the attenuated phenotype is not sufficiently preserved when administered to humans. Study subjects will be observed closely by qualified clinicians, and emergency care will be immediately available to subjects in the isolation unit throughout their stay in the unit. If additional urgent care or resources are needed, the subject will be transported to a local hospital. This hospital will be identified by the investigator prior to study initiation, and appropriate contingencies for isolation of the subject will be made. The study will provide this care to the subject at no cost to the subject.

It is theoretically possible that vaccine virus that is replicating in a subject's upper respiratory tract may be shed and transmitted to those around the subject. If a subject decides to leave the isolation unit prematurely, the subject will be counseled on the theoretical risks to their household contacts and the community. The subject will also be told that local public health authorities might be notified of the subject's premature exiting from the isolation unit and that such authorities might quarantine the subject. A subject who is shedding virus is also potentially infectious to placebo recipients in the isolation facility. All subjects will be monitored closely for infection. (Study staff will be closely monitored outside of the study protocol and use of antivirals prophylactically during the dosing stages may be part of their terms of employment.)

Besides administration of study vaccine or placebo, collection of biological specimens (nasal swab, nasal wick, and blood specimens) may cause some discomfort to subjects. Collection of nasal swab and nasal wick specimens may cause mild discomfort or a tickling sensation in the nasal passages during the collection procedures. Venipuncture is sometimes associated with discomfort or pain, redness, swelling, and/or local hardness at the puncture site.

#### **2.3.1.2 To Participant Privacy**

Personal identifiers, including name, birth date, sex, location/address of residence will be collected and recorded on some study data collection forms. As a result, a potential risk for "loss of confidentiality" exists. To avoid this risk, subjects will be assigned a unique study participant number that will be used to identify the participant and link, using a master linking document, an individual to his/her study data and/or biological specimens. Whenever feasible, use of identifiers will be avoided and the unique study participant numbers will be used instead. Case report forms (CRF) to be sent to the Sponsor or PVS (or their representatives) for data management will contain only unique study participant numbers to identify the participant. Paper-based records will be kept in a secure location and only be accessible to authorized personnel involved in the study. Computer-based files will only be made available to personnel involved in the study through the use of access privileges and passwords. Individual participants will not be identified in any study related reports. Study staff will treat all study data, including subject identifiers and laboratory testing results, as confidential and not to be shared with anyone not authorized to view such data.

Biological specimens will be identified by study participant number; no personal identifiers will be utilized on any biological specimen. Likewise, laboratory reports will utilize only study participant numbers. Biological specimens will be stored in the laboratories of the Research Institute of Influenza (RII) and IEM, as appropriate to where that biological specimen will be tested using assays specified in this study protocol.

Biological specimens will be utilized only for testing in assays specified in this study protocol and approved by overseeing ethical review committees. However, biological specimens may become an extremely valuable resource for future development of improved influenza vaccines against avian and/or pandemic influenza. If written informed consent for long-term storage of any subject's specimens is obtained, those specimens will not be used for

unrelated, future studies without appropriate ethical review and approval and consent from study subjects, if deemed necessary by the overseeing ethical review committees.

### **2.3.2 Known Potential Benefits**

By participating in this study, subjects will be screened by qualified clinicians for health status and through laboratory testing. This screening will be free of cost to the subject and may provide important information to the subject on the subject's health status.

By participating in this study, subjects will contribute information on the safety and immunogenicity of this new vaccine against an avian influenza virus of pandemic potential. Development of new influenza vaccines, such as this LAIV, that are easier and faster to produce, and potentially less expensive, would be a great contribution to global public health.

There are no other known potential benefits to the subject for volunteering for participation in this trial. However, given the recent history of good safety profiles of LAIVs containing avian reassortants, the risk-benefit ratio is considered favorable, especially considering that all subjects will be under constant care of qualified medical personnel.

## **3 Objectives**

### **3.1 Study Objectives**

#### **3.1.1 Primary Objective**

To describe the safety profile of two intranasal doses of LAIV A/17/mallard/Netherlands/00/95 (H7N3) in healthy adults.

#### **3.1.2 Secondary and Exploratory Objectives:**

To describe the post-vaccination serologic immune responses to influenza vaccine.

To describe the post-vaccination shedding of vaccine virus and genetic stability of any shed virus.

Exploratory: To describe the post-vaccination cellular immune responses to influenza vaccine.

### **3.2 Study Outcome Measures**

#### **3.2.1 Primary Outcome Measures**

The safety profile will be parameterized as the proportion of subjects experiencing adverse events (AEs) of the following four categories:

- 
- Immediate reactions occurring within two hours of administration of any dose, measured as observed by study staff or reported by the subject to study staff.
  - Adverse events commonly associated with intranasal vaccination (solicited local and systemic reactions) occurring greater than two hours after administration of any dose of study vaccine or placebo through 7 days following any dose, measured as observed by study staff or reported by the subject to study staff.
  - All other adverse events (including unsolicited events) occurring during the 7 days following any dose, measured as observed by study staff or reported by the subject to study staff. This includes abnormal laboratory findings from blood and urine specimens collected on Days 7 and 35.
  - All serious adverse events (SAEs) occurring within 4 weeks of receipt of any dose, as observed by study staff, reported by the subject to study staff, or noted by the subject on a diary card. This includes abnormal laboratory findings from blood and urine specimens collected on Days 28 (pre-vaccination) and 56.

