After discharge from the isolation unit, subjects will complete diary cards for AEs and use of concomitant medications. Subjects will return to the isolation unit at four weeks (Day 28) after administration of dose one of study vaccine or placebo. At that time, similar procedures will be used for admittance to the isolation unit, for receipt of dose two of study vaccine or placebo and for isolation and follow-up, with the additional procedure of review of interim histories (and diary cards) since first discharge after dose one.

After second discharge from the isolation unit, subjects will again complete diary cards for AEs and use of concomitant medications. Subjects will then return to the study center at four weeks (Day 56) after administration of dose two of study vaccine or placebo for their final study visit. Interim histories (and diary cards) will again be reviewed and final blood and nasal wick specimens will be collected. Women will also undergo a final pregnancy screen. Subjects will complete the study at this time.

For assessment of safety, subjects will be observed for two hours after each administration of study vaccine or placebo. Twice daily (early morning and late afternoon) examination will be also used to assess reactions for 7 days after each administration of study vaccine or placebo. ENT examination will also occur once per day on Days 7, 28, 35 and 56. Subjects will complete diary cards for unsolicited AEs from the day of each discharge until return to the isolation unit for dose two (at Day 28) or until return to the study center for the final study visit at four weeks post dose two (at Day 56). To assess safety, blood and urine specimens will also be collected on days 7, 28 (prior to administration of dose two of study vaccine or placebo), 35 and 56, for testing by routine biochemical and hematological blood tests and by urinalysis by dipstick.

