#### **7.2.19 Day of Final Visit to the Study Center (Day 56)**

1. Subjects will present to the study center. Study staff will confirm subject identity.
2. Study staff will review second subject diary cards and interim histories with the subject and inquire about any new medical events since medical histories were last updated.
3. Blood specimens will be collected for testing a CMP and a CBC with differential, for anti-influenza serologic assays, and for assessing cellular immune responses. Specimen collection information must be documented on the CRF and in specimen collection logs. Any out-of-normal-range result will be recorded as an AE. (If results of blood testing may be sent to the subject if the subject so requests.)
4. A urine specimen will be collected for urinalysis testing via dipstick. Specimen collection information must be documented in the CRF and in specimen collection logs. For women only, the urine specimen will be collected for pregnancy testing. Any out-of-normal-range result will be recorded as an AE.

5. A nasal wick specimen will be collected. Specimen collection information must be documented on the CRF and in specimen collection logs. Nasal wick specimens will be sent to IEM for mucosal anti-influenza IgA testing.
6. A study clinician will perform a physical examination and record the information on the CRF. Results will be reviewed by study staff and with the subject and any AEs that have occurred will be recorded in the appropriate section(s) of the CRF.
7. A study otolaryngologist will perform an ENT examination and record the information on the CRF. Results will be reviewed by study staff and with the subject and any AEs that have occurred will be recorded in the appropriate section(s) of the CRF.
8. Study staff will complete the final visit CRF and terminate the subject's participation in the study.

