### 9.2.3 Serious Adverse Events

All SAEs that occur during the trial will be captured on the CRF.

**Serious Adverse Event:** An SAE is defined as an AE that meets one of the following conditions:

- Death.
- Life threatening (subject at immediate risk of death.) *(The term “life-threatening” in the definition of “serious” refers to an event in which the patient was at risk of death at the time of the event; it does not refer to an event that hypothetically might have caused death if it were more severe).*
- Requires inpatient hospitalization or prolongation of existing hospitalization. *(Continuation of stay in the isolation unit beyond 7 days post-administration of either dose of study vaccine or placebo because of late detected viral shedding in a subject shall not be considered a “prolongation of existing hospitalization” for SAE recording or reporting.)*
- Results in congenital anomaly/birth defect. *(Only in the case of a woman becoming pregnant during the study period after administration of at least one dose of study vaccine. All pregnancies must be followed to term and outcome reported to the Sponsor, PVS and regulatory agencies.)*
- Results in a persistent or significant disability or incapacity.
- Important medical events that might not result in death, be life threatening, or require hospitalization might be considered SAEs when, based upon appropriate medical judgment, the event might jeopardize the well-being of the subject and require medical or surgical intervention to prevent one of the outcomes listed above. *(Medical and scientific judgment should be exercised in deciding whether reporting these events is appropriate.)*

All SAEs occurring within one month of any study vaccination must be reviewed and evaluated by a study clinician (SAE relationship to study vaccine must be evaluated as outlined in Section 9.2.3) and recorded on an SAE form and reported (as specified in Section 9.3). All such SAEs should also be followed until satisfactory resolution or until the investigator deems the event to be chronic or the patient to be stable.

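### Primary safety category 4 puts Day 28 and Day 56 laboratory abnormalities under SAEs with no seriousness limit, and no primary category holds later non-serious clinical AEs

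*Protocol*

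**What the plan says.** Section 3.2.1 expresses the primary safety profile as the proportion of subjects with events in four categories. The same list stands in the Protocol Summary and in Sections 9.1 and 11.3.1.

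- Category 1 is immediate reactions in the first two hours after a dose.
- Category 2 is solicited local and systemic reactions from then on, "through 7 days following any dose, measured as observed by study staff or reported by the subject to study staff".
- Category 3 is "All other adverse events (including unsolicited events) occurring during the 7 days following any dose", followed by: "This includes abnormal laboratory findings from blood and urine specimens collected on Days 7 and 35".
- Category 4 is "All serious adverse events (SAEs) occurring within 4 weeks of receipt of any dose, as observed by study staff", or as reported by the subject, including on the diary card. It is followed by: "This includes abnormal laboratory findings from blood and urine specimens collected on Days 28 (pre-vaccination) and 56".

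Section 9.2.3 defines seriousness by outcome: "An SAE is defined as an AE that meets one of the following conditions". The conditions are death, immediate risk of death, hospitalization and so on. Section 9.2.4 makes an abnormal laboratory value an AE (unless it was Grade 1 at entry and has not worsened) and allows it to be considered an SAE at Grade 4. For Day 56, Section 7.2.19 says "Any out-of-normal-range result will be recorded as an AE", and Section 7.2.10 gives the same instruction for Day 28. Section 4 says "Subjects will complete diary cards for unsolicited AEs from the day of each discharge until return to the isolation unit" for dose two, and then again until the Day 56 visit.

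**The concern.** There are two defects, both in the definition of the only primary outcome.

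First, the laboratory sentence in category 4 carries no qualifier. The twin sentence in category 3 plainly brings all Day 7 and Day 35 abnormalities into the AE category. Read the same way, category 4 brings all Day 28 and Day 56 abnormalities into the SAE category, and the resulting figure would not be an SAE rate in any usual sense.

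Second, categories 1 to 3 end 7 days after a dose and category 4 is for SAEs. A non-serious clinical event in the following three weeks, such as an outpatient respiratory or eye illness after a live virus, has no category. The same is true of a subject kept in isolation past Day 7 or Day 35 because of persistent shedding.

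**Working it through.** The protocol states no hypotheses and no calculated sample size (Section 11.1), so it has no figure of its own to reproduce. The check compares the definitions and then sizes the literal reading.

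**Step 1. Where does an ordinary out-of-range result on Day 28 or Day 56 belong?**

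- Sections 7.2.10 and 7.2.19: an AE.
- Section 9.2.4: an AE, with the Grade 1 baseline exemption; it may be an SAE only at Grade 4.
- Section 9.2.3: an SAE only if it meets a seriousness condition.
- Category 4, read literally: within the SAE proportion.
- Category 4, read as covering serious findings only: not in category 4. It is not in category 3 either, whose laboratory sentence names Days 7 and 35 only. It is therefore in no category.

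Neither reading gives a complete and consistent definition.

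**Step 2. Which days are uncovered for non-serious clinical AEs?** Days 8-27 are 20 days and Days 36-55 are 20 days. Together that is 40 of the 56 days after dose one, 40/56 = 71%. This holds on both readings.

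**Step 3. How large could the literal reading be?** The comprehensive metabolic panel has 14 analytes (Section 8.2.1.3) and the blood count has 15 (Section 8.2.1.4), so 29 per visit and 58 over the two visits. The protocol gives no out-of-range rate, so the rate p per result is an assumption. With independent results, the chance of at least one out-of-range value is 1 - (1 - p)^k:

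| Assumed p | One visit, k = 29 | Both visits, k = 58 | Expected among 30 vaccine recipients |
|---|---|---|---|
| 0.5% | 13.5% | 25.2% | 7.6 |
| 1% | 25.3% | 44.2% | 13.3 |
| 2.5% | 52.0% | 77.0% | 23.1 |
| 5% | 77.4% | 94.9% | 28.5 |

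The arm sizes follow from Section 4: 9 + 21 = 30 vaccine and 3 + 7 = 10 placebo. The 7 dipstick items are left out; adding them raises the figures.

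**Step 4. How far does correlation lower this?** A simulation with a common correlation among the 29 analytes, at one visit and p = 5%, gave 64.9% at correlation 0.3 and 49.8% at 0.5, against 77.4% under independence. The Grade 1 baseline exemption would lower the figures further, by an amount the protocol does not allow one to compute.

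**Step 5. What would the category show if it held only true SAEs and there were none?** The exact 95% upper limit for 0 of n is 1 - 0.025^(1/n). For 0/30 it is 11.6%; for 0/10 it is 30.8%.

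**The case against.** The best defence is that the laboratory sentence qualifies the SAEs named just before it, so only serious laboratory findings are meant. Section 8.1.1 supports this: a laboratory finding might be categorized as an SAE, with a pointer to 9.2.3. So does the Grade 4 provision in 9.2.4. No visit instruction tells the site to record an ordinary out-of-range value as an SAE. This stands as far as it goes. A reader might infer that the reported SAE rate will be inflated, and the documents do not support that as a fact; it follows only from the literal wording. But the narrow reading leaves the non-serious Day 28 and Day 56 abnormalities without a category, so it moves the defect and does not remove it.

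A reader might also infer that late non-serious AEs will go unreported. That is not supported either. Section 9.2.2 has all AEs during the study assessed and recorded, and Section 11.3.1 promises counts of all events, with percentages and exact intervals. The gap lies in what the primary proportions cover, not in data collection or overall reporting.

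The size is also open to challenge. Blood-count indices are linked arithmetically, the two visits are repeat measures on the same person, and Grade 2 or higher screening results exclude entry. All of this is fair, and the upper end of the range should not be taken as a forecast.

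Finally, the trial is descriptive, no prespecified halting rule depends on this proportion, and Section 11.3 defers table shells to a later plan. That limits the consequences. It does not repair the text: a plan that follows the protocol inherits the contradiction, and one that departs from it changes the primary outcome.

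**Conclusion.** The point holds as a defect in the primary outcome definition, repeated in four places. The contradiction in category 4 and the missing window for non-serious clinical AEs (40 of 56 days) follow from the text alone and need no assumption.

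The numerical size is conditional. It applies only if the laboratory sentence is read literally, and it depends on assumed out-of-range rates and on independence. Within those limits, roughly 13 to 29 of 30 vaccine recipients at rates of 1% to 5% (about 8 at 0.5%) could enter the SAE proportion without a serious event, where the proper result would be 0/30. Correlation and the baseline exemption reduce these numbers. At the rates shown, the literal proportion would still not be readable as an SAE rate.

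**What to change.** Make the same change in the Protocol Summary and in Sections 3.2.1, 9.1 and 11.3.1.

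1. Limit category 4 to events, laboratory findings included, that meet the SAE definition in Section 9.2.3, and delete the unqualified laboratory sentence. Sections 9.2.3 and 9.2.4 must be reconciled first, so that it is clear when a laboratory value counts as serious. Section 9.2.4 also calls Grade 4 severe, whereas the general scale in Section 9.2.2 uses that word for Grade 3 and calls Grade 4 life threatening; the labels should be aligned at the same time.
2. Add a category: the proportion of subjects with non-serious AEs from after Day 7 to 4 weeks after each dose, including Day 28 (pre-dose) and Day 56 laboratory abnormalities. Report it beside the 7-day category, with the same exact intervals.

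The cost is a wording amendment, carried into the analysis plan, and one extra table. All the data are already collected.
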